## 5.2 Data analysis: Primary study outcomes

### 5.2.1 Primary study outcome 1 – Minimum detectable risk

The minimum detectable risk that can be detected for each health outcome in a future study will be quantified for each GAIA case definition. The minimum detectable risk will be the minimum detectable odds ratio (OR) in a case-control study design and the minimum detectable relative risk (RR) in a cohort study design. This information will be useful to establish the sample size that can be achieved in a one-year period for a specific health outcome in future studies, and the minimum detectable risk that could be achieved. Note that the data collected on maternal vaccination during the study will not be used in this calculation, as this data were collected solely to assess the applicability, and not to assess risk associated with maternal vaccinations currently in use.

For the case-control study design, the minimum detectable OR for each health outcome will be calculated based on:

- Number of cases classified during the study period,
- Different theoretical levels of exposure (maternal vaccination) among cases and controls,
- The ratio of cases to controls,
- 80% power and 95% confidence level,
- Per year of study duration.

For the cohort study design, the minimum detectable RR for each health outcome will be calculated based on:

- Different theoretical percentages of exposed (maternal vaccination) and non-exposed (no maternal vaccination) with each health outcome,
- Different theoretical levels of exposed to unexposed ratio,
- 80% power and 95% confidence level,
- Per year of study duration

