## 2.1 Rationale

The goal of this prospective study is to estimate the minimum detectable risk for selected neonatal outcomes (neonatal death, neonatal infection, congenital microcephaly, low birth weight, preterm birth, small for gestational age, and stillbirth) in each study site using standardised case definitions and to assess the applicability of GAIA case definitions in LMICs, in order to inform future vaccine safety studies.

The use of GAIA case definitions can be challenging in LMICs, as the proposed criteria for some definitions can exceed the clinical capacity of some sites. The study will assess the applicability of GAIA definition for health outcomes. The health outcomes were selected based on relevance and perceived complexity of data collection. For future vaccine safety

study, sites should be able to link vaccination status information of pregnant women to obstetric and neonatal outcomes. Hence the project will also assess the current sites' capacity for data identification and collection on maternal immunisation status.

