#### 4.7.8 Ascertainment of vaccine exposure

To assess whether sites are able to determine whether a vaccine had been administered during pregnancy or within 30 days prior to the last menstrual period (LMP). Maternal vaccination status for tetanus or any other vaccines administered during pregnancy will be ascertained for all mothers of identified cases with the health outcome of interest.

A mother who has any mention of maternal vaccination will be considered vaccinated (exposed). This could be a formal recording of vaccination or any other mention in the documents available to the sites.

A mother who has documented evidence of absence of maternal vaccination will be considered non-vaccinated (non-exposed).

Any mother without any indication will be considered to have exposure status 'unknown'.

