### 5.2.2.2 Exposure: level of certainty for maternal immunisation

The applicability of the GAIA definition for maternal immunization will be assessed by calculating the proportion of vaccination mothers identified that can be classified according to the GAIA definition.

The denominator will be the number of vaccination mothers identified; the numerator will be the number of vaccination mothers identified that can be classified according to the GAIA definition.

The applicability of the GAIA definition will be reported overall, and stratified by site/country/region, by health facility level (primary/secondary/tertiary) and by type of data (paper vs. electronic).

The proportion of all mothers whose maternal vaccination status was assessed as exposed, non-exposed and unknown will be described.

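### The minimum detectable odds ratio counts every classified case and so assumes, without saying it, that vaccination status is known for all of them

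*Protocol*

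**What the plan says.** Section 5.2.1 lists the inputs to the minimum detectable OR of a future case-control study. The input that sets the sample size is "Number of cases classified during the study period". The others are a range of assumed exposure levels, a control ratio, power of 80% with 95% confidence, and a duration of one year. A footnote in section 5.3.1.1 explains that classified means classified by the GAIA case definitions. Knowing the mother's vaccination status is not a condition.

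The same section adds: "Note that the data collected on maternal vaccination during the study will not be used in this calculation". The reason given is that these data serve to assess applicability, not the risk from vaccines now in use.

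Section 4.7.8 sets three exposure states. Any mention of vaccination makes a mother exposed, and documented absence makes her non-exposed. For the rest, "Any mother without any indication will be considered to have exposure status 'unknown". The maternal immunization form in Annex V applies the same rule: no is allowed only with documented evidence. Section 5.2.2.2 adds: "The proportion of all mothers whose maternal vaccination status was assessed as exposed, non-exposed and unknown will be described". Section 5.5 rules out imputation.

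On future vaccine safety studies, section 2.1 states that "sites should be able to link vaccination status information of pregnant women to obstetric and neonatal outcomes", and that the project will therefore also assess this capacity at the sites.

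**The concern.** Primary outcome 1 is meant to tell planners what sample size, and hence what risk, a site could reach in one year. An exposure OR comes from a two-by-two table of case status against exposure, and a case whose exposure is unknown has no cell in it. Section 5.2.1 nevertheless counts that case in full towards 80% power.

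The stated reason for setting the vaccination data aside covers observed vaccine prevalence and any vaccine-outcome association. It does not cover how often status can be determined at all. That is a measure of site capacity, which section 2.1 says the project will assess and section 5.2.2.2 reports. The two primary outputs are left unconnected, and the assumption of complete ascertainment is not stated. A planner who takes the OR at face value would start a study with less than the nominal power wherever some exposures cannot be ascertained.

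**Working it through.** **No figure to reproduce.** The protocol states no minimum detectable OR, exposure level, control ratio or unknown share. The check is therefore one of direction, with size shown over an assumed range.

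**Inputs.**
- From the protocol: 80% power and 95% confidence (section 5.2.1), taken as two-sided 5%; n = 100 cases for illustration, the target per outcome and site in section 5.1.2.
- Assumed: control exposure p0 = 50%, one control per case, unknown share u = 20%, 30% or 50%.

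**Formulas.** Case exposure is p1 = OR·p0 / (1 + p0(OR − 1)). With n1 cases and n0 controls of known exposure, and p̄ the exposure pooled over both groups:
- se0 = √[p̄(1 − p̄)(1/n1 + 1/n0)]
- se1 = √[p1(1 − p1)/n1 + p0(1 − p0)/n0]
- power = Φ[(p1 − p0 − 1.96·se0)/se1]

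The minimum detectable OR is the value giving power 0.80.

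**All 100 cases counted.** At OR 2.26, p1 = 1.13/1.63 = 0.693 and p̄ = 0.597. Then se0 = 0.0694, se1 = 0.0680, and (0.1933 − 0.1360)/0.0680 = 0.84, so power is 80%.

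**30% unknown, same OR.**
- 70 cases and 70 controls: se0 = 0.0829, se1 = 0.0813; (0.1933 − 0.1625)/0.0813 = 0.38, power 65%.
- 70 cases and 100 controls: p̄ = 0.580, se0 = 0.0769, se1 = 0.0744; (0.1933 − 0.1508)/0.0744 = 0.57, power 72%.

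**Solved over the range (100 classified cases, 1:1, p0 = 50%).**

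| Unknown share | OR, controls lost in proportion | Power at OR 2.26 | OR, 100 controls kept | Power at OR 2.26 |
|---|---|---|---|---|
| 0% | 2.26 | 80% | 2.26 | 80% |
| 20% | 2.51 | 71% | 2.39 | 75% |
| 30% | 2.68 | 65% | 2.48 | 72% |
| 50% | 3.29 | 50% | 2.77 | 62% |

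**Other settings (controls lost in proportion; 0%, 20%, 30%, 50% unknown).**
- 100 cases, four controls per case, p0 = 50%: 1.89, 2.05, 2.16, 2.52.
- 500 cases, 1:1, p0 = 50%: 1.43, 1.49, 1.53, 1.66.
- 100 cases, 1:1, p0 = 80%: 3.53, 4.41, 5.21, 9.74.

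At 30% unknown and p0 = 50%, the rise is 0.42 for 100 cases at 1:1 (2.68 − 2.26), 0.27 at 1:4 (2.16 − 1.89) and 0.10 for 500 cases at 1:1 (1.53 − 1.43). The direction is the same throughout; the size depends on inputs the protocol does not fix.

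**The case against.** The strongest reply is that section 5.2.1 makes an open choice of scope. It projects a future study at theoretical exposure levels and says that current vaccination data are left out. A future study of a new vaccine may record exposure better or worse than today's routine records do, so today's unknown share is a debatable input. This stands, and it is a reason not to replace the all-classified figure. It does not excuse leaving the assumption unstated, since the protocol nowhere says that future ascertainment will be complete.

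A second reply is that section 5.2.2.2 reports the unknown share, so readers can make the adjustment themselves. They can in part, but the calculation is not a simple rescaling and the section does not prompt them to do it.

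Third, section 6 treats mothers with no evidence or history of vaccination as not vaccinated. Under that rule such cases would enter the table. But it conflicts with section 4.7.8, and section 6 itself concedes false-negative exposures. Counting misclassified cases does not restore the stated power.

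Three stronger readings are tempting, and the documents do not support them:
- *The unknown share must be large.* Section 4.7.8 requires documentation for non-exposed but defines exposed very broadly, as any mention. No figure is given.
- *Sites will be misranked.* Nothing in the protocol ranks sites.
- *The known-status count should replace the case count, and the same share be applied to the cohort.* Section 4.7.8 ascertains status only for mothers of identified cases, and the delivery register in section 4.6 holds no vaccination field. The share in controls and in the whole cohort is therefore not observed.

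**Conclusion.** The point holds in a limited form. Section 5.2.1 assumes complete exposure ascertainment without saying so, although the protocol defines and measures the opposite. If ascertainment in a future study resembles current practice, the reported OR is too favourable for any unknown share above zero. In the illustrative setting, 2.26 becomes 2.39 to 2.51 at 20% unknown, 2.48 to 2.68 at 30% and 2.77 to 3.29 at 50%; in each pair the lower value keeps all 100 controls and the higher loses them in proportion.

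These sizes rest on assumed unknown shares, 100 cases, one control per case and 50% control exposure, none of which the protocol fixes for this calculation. The absolute effect is smaller with more cases or controls and larger at 80% control exposure. A reader might infer that the primary outcome is invalid or must be replaced. It is not: the all-classified OR is a legitimate best case, provided it is labelled as one.

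**What to change.** 1. In section 5.2.1, keep the OR based on all classified cases and state that it assumes exposure is ascertained for every case and control.
2. Beside it, report per site and outcome the OR with the case count multiplied by the observed share of case mothers whose status is exposed or non-exposed under section 4.7.8.
3. For controls, and for the cohort relative risk, show results over a range of known-status shares, labelled as an assumption because status is not collected there.
4. Narrow the note in section 5.2.1 so that it bars observed vaccine prevalence and vaccine-outcome association, but not the completeness of exposure status.
5. Reconcile section 6 with section 4.7.8 on mothers without any evidence of vaccination.

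The cost is some wording and one extra count per site and outcome from data already collected. The downside is a second, less favourable figure that assumes current ascertainment carries over to the future study.

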In response to the call of WHO for a globally concerted approach to monitor the safety of vaccine in pregnancy, the Global Alignment of Immunization Safety Assessment in Pregnancy (GAIA) project was launched in 2015. The aim of GAIA, managed by the Brighton Collaboration [9], was to improve generated data to facilitate data comparability and interpretation across surveillance systems, ultimately leading to strengthened programs of immunization in pregnancy [10, 11]. To this end, standardized definitions for obstetric and neonatal health outcomes were developed. The purpose of this harmonization and standardization is to increase the ability to conduct meaningful comparisons of safety data across studies [7, 9]. Within each case definition, multiple 'Levels of diagnostic certainty' are recognized, so that the definitions are globally applicable for all immunization safety purposes and in settings with different levels of diagnostic capacities [9].

As several promising vaccines in development would be of great benefit specifically for women and children in low and middle-income countries (LMICs), due to higher perinatal and infant mortality rates, it is now critical that those countries develop vaccine safety monitoring beyond passive surveillance, in this specific population.

In an effort to address WHO's Global Vaccine Safety Blueprint (5) strategic goal of enhanced pharmacovigilance capacity, the Global Vaccine Safety Initiative (6), through its WHO secretariat, tested the development of a global network of hospital-based sentinel sites of LMICs across the WHO regions for vaccine safety signal verification and hypothesis testing. The aim of the project was to identify optimal models and processes for establishment and operationalization of such a network. The lessons learnt from this proof of concept project will be integrated in the development of this study [12].

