#### 4.10 Case classification

Identified cases and exposures will be classified using the Brighton Collaboration ABC tool (Automatic Brighton Classification) [20] according to the levels of diagnostic certainty present in the GAIA definitions (Level 1-3, and Level 4-5 when applicable).

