## 5.3 Secondary study outcomes

### 5.3.1 Secondary study outcome 1 – Proportion of cases classified by level

#### 5.3.1.1 Health outcomes

For each health outcome, the proportion of cases that can be classified according to each GAIA case definition level will be assessed.

*Proportion of cases identified that can be classified by level*

- For each health outcome, the proportion of cases identified that can be classified according to each GAIA case definition level will be assessed.

---

 In this document, 'classified' will mean 'classified according to the GAIA case definitions'

- The denominator will be the number of cases *identified* for one outcome; the numerator will be the number of classified cases for each level of the GAIA case definition.

*Proportion of cases classified by level*

- For each health outcome, the proportion of cases classified by level will be calculated.
- The denominator will be the number of cases *classified* for one outcome for all levels; the numerator will be the number of classified cases for each level of the GAIA case definition.

These proportions will be reported overall, and stratified by site/country/region, and by health facility level (primary/secondary/tertiary).

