#### Level 5 of diagnostic certainty

- No evidence of SGA or a confirmed diagnosis other than SGA

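### The case-control minimum detectable OR in Protocol 5.2.1 pools classified cases of every certainty level, does not exclude SGA Level 5 (a non-case category), and leaves unclear whether the count is capped

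*Protocol*

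**What the plan says.** The minimum detectable risk is a primary outcome. Protocol 5.2.1 says that it "will be quantified for each GAIA case definition", that is, per outcome and not per level. For the case-control design the only case input is the "Number of cases classified during the study period". It is combined with theoretical exposure levels, the ratio of cases to controls, 80% power and 95% confidence.

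Classified carries no minimum level. The footnote in 5.3.1.1 equates it with classified under the GAIA definitions, and the same section counts classified cases "for one outcome for all levels". Section 4.10 lists the levels assigned as "Level 1-3, and Level 4-5 when applicable". In Annex III, SGA Level 5 reads "No evidence of SGA or a confirmed diagnosis other than SGA".

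The level split is planned elsewhere. In 5.3.1.1, "the numerator will be the number of classified cases for each level of the GAIA case definition", reported overall and by site. Section 5.2.1 does not refer to those counts.

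On how many cases enter, the protocol says two things. Section 5.1.1, on this same outcome, includes all cases identified. Sections 4.3, 4.9 and 5.1.2 stop recruitment at 100 cases per outcome per site.

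**The concern.** The levels exist to separate degrees of certainty; section 2 notes that "Within each case definition, multiple 'Levels of diagnostic certainty' are recognized". For some outcomes they are far apart. In Annex III, Level 1 bloodstream infection rests on an identified organism, while Level 3 needs two or more clinical criteria. Level 4 microcephaly can rest on inspection without a head measurement. Level 4 SGA can rest on a baby noted as small with no recorded weight. Level 5 SGA is not a case at all.

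Section 5.2.1 intends the result to show the sample size and detectable risk that future studies could achieve in a year. Such a study would either restrict to higher levels and have fewer cases, or keep all levels and accept some false cases. With the same starting count, both raise the true OR needed for 80% power. A planner who reads a pooled OR without its level set could choose a study that is too small.

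**Working it through.** **The protocol's own figure.** The protocol states no minimum detectable OR. Its nearest sample-size figure is the 97 cases in Table 1 behind the 100-case target: 1.96² × 0.5 × 0.5 / 0.10² = 96.04, rounded up to 97. It reproduces.

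**Inputs for the OR.** Power of 80% and 95% confidence come from 5.2.1, the latter read as two-sided 5%. The 100 cases are the per-site target in 5.1.2. Exposure, control ratio, level shares and shares of true cases are assumptions.

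**Formulas.** With p0 the exposure in controls, exposure in true cases is p1 = p0·OR / [1 + p0(OR − 1)]. For 1:1 controls and p̄ = (p1 + p0)/2,

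n = [1.96·√(2p̄(1−p̄)) + 0.842·√(p1(1−p1) + p0(1−p0))]² / (p1 − p0)², solved for OR.

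**All 100 cases usable, p0 = 0.5.** OR = 2.26 gives p1 = 2.26/3.26 = 0.6933 and p̄ = 0.5966. The numerator is (1.360 + 0.573)² ≈ 3.735, and 3.735 / 0.1933² ≈ 100.

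**Restriction to higher levels.** If half qualify (n = 50), OR = 3.29: p1 = 3.29/4.29 = 0.7669, the numerator is (1.336 + 0.551)² ≈ 3.561, and 3.561 / 0.2669² ≈ 50. If 75% or 25% qualify, the OR is 2.59 or 6.19.

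**All 100 kept, some false.** Give false cases the controls' exposure. Observed case exposure is then p0 + t(p1 − p0), where t is the share of true cases. It must still reach 0.6933, so p1 = 0.5 + 0.1933/t.
- t = 0.9: p1 = 0.715, OR 2.51
- t = 0.8: p1 = 0.742, OR 2.87
- t = 0.7: p1 = 0.776, OR 3.47

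**Sensitivity to the assumptions.** Minimum detectable OR with 1:1 controls:

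| Exposure in controls | 100 cases | 50 cases | 25 cases |
|---|---|---|---|
| 10% | 2.99 | 4.37 | 7.20 |
| 30% | 2.27 | 3.15 | 5.12 |
| 50% | 2.26 | 3.29 | 6.19 |
| 70% | 2.69 | 4.78 | 24.4 |
| 90% | 10.8 | not reachable | not reachable |

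With 1:4 controls and 50% exposure, 100 / 50 / 25 cases give 1.89 / 2.52 / 3.93. At 30% to 50% exposure, halving the usable cases, or having 70% true cases, cuts power at the pooled OR from 80% to about 50%.

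**Effect of the cap (1:1, 50% exposure).** Suppose a site has 400 cases a year, half at higher levels. A count capped at 100 gives 2.26. A one-year restricted study there would have 400 × 0.5 = 200 cases and an OR of 1.76, so 2.26 is too unfavourable. The two effects balance when annual cases × higher-level share = 100. With 200 cases a year and a quarter at higher levels, 50 are usable and 2.26 is again too favourable against 3.29.

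**The case against.** The strongest reply is that tables by level are matter for the statistical analysis plan, which is not shown, and that nothing in 5.2.1 forbids them. The level counts are planned, so a reader could derive a level-restricted OR. That lowers the stakes. It does not remove the point, because the protocol itself fixes the case input for a primary outcome, and fixes it without a level set.

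A reader might infer that the pooled OR is always too favourable. The documents do not support this: the cap can reverse the direction at busy sites, as shown above.

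A reader might equate low level with false case. For low birth weight, Levels 1 to 3 all require a weight below 2500 g and differ mainly in scale and timing. Preterm levels differ in dating method, and neonatal death levels mainly in certainty of gestational age and who confirmed the death. Pooling is more defensible there. The protocol gives no share of true cases by level.

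A reader might also suppose that Levels 3 and 4 dominate at low-capacity sites. No level distribution is given, and in Annex III preterm birth, neonatal death and neonatal infection have no Level 4. Nor does the protocol say that SGA Level 5 records will be counted as cases; its wording only fails to exclude them.

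Size also depends on scale. If all 25 sites reached 100 cases (25 × 100 = 2,500; 1:1, 50% exposure), the pooled OR is 1.17, against 1.23 with 60% retained and 1.26 with 70% true cases. Those are small shifts. The goal in 2.1 is per site, however, where counts are smaller.

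**Conclusion.** The point holds in a limited form. The case count in 5.2.1 pools all GAIA levels and does not exclude a non-case category. For a given count, the OR is then smaller than a study restricted to higher levels, or one containing false cases, could detect. At 100 cases the change is from 2.26 to 3.29 if half qualify, or to 2.87 if 80% are true cases. Both figures assume 1:1 controls and 50% exposure, and the second also assumes that false cases have the controls' exposure. The shares are assumed, so the actual size cannot be derived from the protocol.

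The direction is not general, because the protocol leaves open whether the count is capped. Only the case-control OR is affected: the inputs listed for the cohort relative risk are theoretical percentages and do not use the classified count.

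**What to change.** In 5.2.1:
- Exclude SGA Level 5 from the case count.
- Report the minimum detectable OR for each outcome cumulatively by level (Level 1; 1–2; 1–3; all case levels), using the 5.3.1.1 counts, and label the level set of each OR.
- State whether the count is the capped recruited number or is scaled to all identified cases, and reconcile 5.1.1 with 4.3, 4.9 and 5.1.2. Scaling is feasible because section 4.9 registers outcomes for every delivery; the share classified at each level among recruited cases could be applied to that total.

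Rows at assumed shares of true cases (for example 100, 90, 80 and 70%) are an optional sensitivity analysis. They are useful mainly for outcomes whose lower levels rest on clinical signs or inspection.

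The cost is a few more table rows and a change of wording, with no new data. Below the cap, the quoted ORs become less favourable.
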